### Sample size considerations and statistical analysis

The trial is powered to assess the superiority of HRT when compared with CRT. Power calculations are based on an absolute increase in bPFS of 15% (from 50 to 65%) at 5 years following HRT compared with CRT according to the dose-response relationship described by King [9]. By postulating a minimum 5-year follow-up period and allowing 5% for loss, at least 144 patients per treatment arm (288 patients in total) are required, which achieves 80% power, with a two-sided *α* of 0.05. Subgroup analyses will be performed based on the risk group (intermediate vs. high-risk group), RT field size (prostate bed only vs. elective pelvic nodal irradiation), and use of ADT.

Statistical analysis will be conducted according to the intention-to-treat approach. Survival data, PSA value, toxicity, and QoL information will be collected even though participants discontinue the planned treatment. Multiple imputation method will be used for handling missing data. The chi-square test and Student’s *t* test will be used for categorical and continuous variables of patient characteristics, respectively. Time to biochemical progression will be calculated from the end of RT. The Kaplan–Meier method will be applied to estimate bPFS curves, and the log-rank test will be used to compare the curves between the two study arms. The Kaplan-Meier method and log-rank test will be used to investigate DMFS and CSS. Acute toxicity outcomes and QoL will be estimated using the chi-square test, and late toxicity outcomes will be determined using the Kaplan-Meier method.

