Gladwish [29]	Phase I/II	Salv. (26)/Adj. (4)	51	3	65.57	66.3	102
Macchia [28]	Phase I/II	Salv. (18)/Adj. (106)	62.5	2.5	71.43	78.13	114.58
This study	Phase III	Salv. (288)	65	2.5	74.29	81.25	119.17

*EQD2* equivalent dose in 2-Gy fractions, *BED* biologically equivalent dose, *Salv.* salvage, *Adj.* adjuvant

^a^*α*/*β* ratio for prostate cancer is 1.5, 10 for early-responding normal tissue, and 3 for late-responding normal tissue

^b^Median

^c^Salvage

**Table 2 Tab2:** Literature review of hypofractionated radiotherapy outcomes for the treatment of prostate cancer in the postoperative setting

Study (ref.)	Median follow-up, months	bPFS, %	Toxicity scoring system	Acute toxicity, %		Late toxicity, %	
				GU	GI	GU	GI
Tandberg [30]	38.6	78.4^a^ (4 years)	CTCAE v4.0^b^/RTOG^c^	≥ G2: 22; G3: 1^d^	G2: 5; ≥ G3: 0	G2: 39; ≥ G3: 11	G2:10; G3: 1^d^
Kruser [33]	32.4	67 (4 years)	RTOG	G2: 6.4; G3: 1^d^	G2: 14; ≥ G3: 0	G2: 15; ≥ G3: 0	G2: 4; ≥ G3: 0
Lewis [31]	48	75 (4 years)	CTCAE v4.0^b^/RTOG^c^	G2: 4; ≥ G3: 0	G2: 4; ≥ G3: 0	G2: 39; G3: 28	≥ G3: 2^d^
Cuccia [32]	30	73 (3 years)	CTCAE v4.0	G2: 4; ≥ G3: 0	G2: 18; ≥ G3: 0	G2: 2.6; G3: 2.6	G2: 6.6; ≥ G3: 0
Barra [34]	15.5	Not reported	CTCAE v4.0^b^/RTOG^c^	≥ G2: 0	≥ G2: 0	G2: 3.3; G3: 3.3	≥ G2: 0
Alongi [35]	22.8	Not reported	RTOG	G2: 10; ≥ G3: 0	G2: 20; ≥ G3: 0	G2: 8; G3: 3	≥ G2: 0
Saldi [27]	27	Not reported	CTCAE v4.0	G2: 8.9; ≥ G3: 0	G2: 9.8; ≥ G3: 0	Not reported	Not reported
Katayama [26]	Not reported	Not reported	CTCAE v4.0	≥ G2: 0	G2: 17.9; ≥ G3: 0	Not reported	Not reported
Gladwish [29]	24	Not reported	CTCAE v3.0^b^/RTOG^c^	G2: 3; G3: 3	≥ G2: 0	≥ G2: 1^d^	≥ G2: 2^d^
Macchia [28]	30	86.5 (5 years)	RTOG	G2: 17.7; G4: 1^d^	G2: 24.2; ≥ G3: 0	≥ G2: 7.3	≥ G2: 1.1

*bPFS* biochemical progression-free survival, *GU* Genitourinary, *GI* gastrointestinal

^a^Patients with a 12-month minimum follow-up were analyzed for bPFS

^b^Acute

^c^Late

^d^Number of patients

The protocol of the Salvage hypofractionated accelerated versus standard radiotherapy for biochemical recurrence after radical prostatectomy (SHARE) study is outlined here. This prospective, randomized, multi-institutional trial is designed to assess whether HRT improves biochemical control versus CRT without increasing treatment toxicity in prostate cancer patients with biochemical recurrence after radical prostatectomy. This study uses two RT dose schemes, HRT (65 Gy in 2.5-Gy fractions) versus CRT (66 Gy in 2-Gy fractions).

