### Dropout criteria

Patients shall be free to withdraw their consent once given but shall not suffer any disadvantage in terms of medical practice for the withdrawal. Any participant with medical problems or unexpected serious complications occurring during treatment or follow-up period that means the study protocol cannot be completed will be analyzed on an intention-to-treat basis.

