### Assessment of primary and secondary endpoints

The primary endpoint is to investigate whether HRT improves 5-year bPFS versus CRT in patients with biochemical recurrence after radical prostatectomy. Biochemical progression-free survival is counted from the date of the salvage radiotherapy to biochemical progression, clinical progression, or death of any cause. Biochemical progression after RT is defined as detectable PSA after salvage RT. Secondary endpoints are to compare acute and late toxicities based on CTCAE v5.0 and QoL and to determine 5-year distant metastasis-free survival (DMFS) and cancer-specific survival (CSS).

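### The intention-to-treat rule makes no exception for toxicity, so men who never start RT or receive the other schedule could modestly narrow the toxicity difference (minor)

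*Protocol article*

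**What the plan says.** Under Sample size considerations and statistical analysis, the protocol article states "Statistical analysis will be conducted according to the intention-to-treat approach". The sentence is not restricted to efficacy. The next one reads "Survival data, PSA value, toxicity, and QoL information will be collected even though participants discontinue the planned treatment". The same paragraph assigns missing data to multiple imputation and then gives the toxicity methods: "Acute toxicity outcomes and QoL will be estimated using the chi-square test", with Kaplan-Meier for late toxicity.

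Under Dropout criteria, men whose medical problems or complications arise during treatment or follow-up, in a way "that means the study protocol cannot be completed will be analyzed on an intention-to-treat basis", also come under intention to treat.

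The Background gives the aim as finding out whether "HRT improves biochemical control versus CRT without increasing treatment toxicity". The endpoint section is more neutral: "Secondary endpoints are to compare acute and late toxicities based on CTCAE v5.0 and QoL". The article states no toxicity margin and no separate toxicity population.

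**The concern.** Intention to treat is the right rule for a superiority claim on bPFS, where dilution by non-adherence works against the new treatment. For toxicity the direction reverses. If HRT is more toxic, a man allocated to HRT who is never irradiated, or who receives 2-Gy fractions, lowers the HRT rate. A man allocated to CRT who receives 2.5-Gy fractions raises the CRT rate. Both kinds of deviation bring the arms closer, which suits a trial hoping to report better control at no cost in toxicity.

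The article gives reason to expect a difference. Its Discussion cites a retrospective comparison with more acute GU toxicity after HRT, and its Table 3 gives HRT the higher biologically effective dose for late-responding tissue (119.17 against 110 Gy). What is at stake is the estimated size of a secondary comparison. The primary result is not involved.

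**Working it through.** The plan gives no figure for the toxicity comparison, so there is none to reproduce. The check is how far the stated rule could move a plausible difference.

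**Inputs from the article**
- Acute grade 2 or higher GU toxicity: 22% after HRT and 8% after CRT (Discussion, retrospective comparison of 167 and 294 men).
- Group size: 144 per arm (set for bPFS and used here only as the denominator).
- Two-sided α of 0.05.

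**Assumptions, not in the article**
- A fraction f of each arm never starts RT.
- A fraction s receives the other schedule, either in both arms or from HRT to CRT only.
- Men who never start have no RT toxicity.

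**Formulas, by allocated arm**
- HRT rate = (1 − f − s) × 0.22 + s × 0.08
- CRT rate, switching both ways = (1 − f − s) × 0.08 + s × 0.22
- CRT rate, switching from HRT only = (1 − f) × 0.08
- Difference = 0.14 × (1 − f − 2s) with switching both ways, or 0.14 × (1 − f − s) with switching from HRT only
- Power comes from the usual two-proportion normal approximation (pooled variance under the null). With no deviation: (0.14 − 1.96 × 0.0421) / 0.0413 = 1.39, which is a power of 91.8%.

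**Results**

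| Assumed deviation | HRT | CRT | Difference (points) | Power |
|---|---|---|---|---|
| None | 22.0% | 8.0% | 14.0 | 91.8% |
| 2% never start | 21.6% | 7.8% | 13.7 | 91.2% |
| 5% never start | 20.9% | 7.6% | 13.3 | 90.2% |
| 2% switch both ways | 21.7% | 8.3% | 13.4 | 89.5% |
| 5% switch both ways | 21.3% | 8.7% | 12.6 | 85.3% |
| 5% switch HRT to CRT only | 21.3% | 8.0% | 13.3 | 89.5% |
| 5% never start and 5% HRT to CRT only | 20.2% | 7.6% | 12.6 | 87.5% |
| 5% never start and 5% switch both ways | 20.2% | 8.3% | 11.9 | 82.7% |

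Worked example, last row: HRT = 0.90 × 0.22 + 0.05 × 0.08 = 0.202; CRT = 0.90 × 0.08 + 0.05 × 0.22 = 0.083; difference 0.119.

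**Scale**
- The 95% confidence interval for a 22% against 8% difference has a half-width of 1.96 × √[(0.22 × 0.78 + 0.08 × 0.92) / 144] = 8.1 points. The largest shift in the table is 2.1 points.
- Non-start at the same rate in both arms leaves the risk ratio unchanged: 20.9 / 7.6 = 2.75 = 22 / 8.
- Leaving out 5% non-starters restores the 14.0 points but leaves about 137 men per arm, and power is 90.5% against 90.2% with them included. The gain is an undiluted estimate and hardly any power.

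**The case against.** The strongest reply is that this is a condensed article. A general intention-to-treat sentence does not define the toxicity denominator, and a safety population is commonly left to the full protocol or analysis plan. That stands to this extent: the lack of a named safety set is no fault in itself. The point rests on the rule that is stated, which is unrestricted and shares a paragraph with the toxicity tests.

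Four stronger readings are tempting, and the documents do not support them:
- *Never-irradiated men are scored as free of toxicity.* The article does not say so. Assessments are scheduled around RT, so such a man has no on-treatment visits, and the stated multiple imputation might apply to him. The non-start rows above therefore rest on an assumption.
- *The dropout section confirms the problem.* It covers complications during treatment or follow-up and says nothing about non-starters or switchers.
- *The rule would conceal excess HRT toxicity.* No deviation rate is given; the only 5% in the analysis section is an allowance for loss. At the assumed rates a 22% against 8% signal stays plainly visible.
- *Toxicity is a non-inferiority claim tested in the wrong population.* The wording about no added toxicity is a Background aim; the endpoint is a secondary comparison. Dilution flatters HRT only if a small or non-significant difference is later read as no increase, and no choice of population cures that misreading.

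It is also fair to say that intention to treat protects something. Men who stop or change HRT because of toxicity stay in the HRT arm, and their data are still collected. Grouping by treatment can introduce selection: if men with poor urinary function were moved from HRT to 2-Gy fractions before starting, high-risk men would enter the CRT group and HRT toxicity could be understated. That is why neither analysis should stand alone.

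**Conclusion.** The point holds as a minor one. The stated rule covers toxicity by its plain wording, and any dilution runs towards the hoped-for conclusion. Its size cannot be known from the article. With 22% against 8% and assumed non-start, switching or both at 2% to 5%, the difference falls from 14.0 to between 11.9 and 13.7 points. Power stays at 83% or above, and non-start alone costs at most about 2 points of power. The illustration concerns acute GU toxicity, uses rates from a retrospective cohort, and takes non-starters as free of RT toxicity. For late toxicity the direction is the same, but no size was calculated. The bPFS analysis and the sample size are untouched.

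**What to change.** In the analysis section, limit the intention-to-treat sentence to bPFS, DMFS and CSS. Name quality of life there too, so that it is not left without a population; this point does not touch it. Then add: acute and late toxicity are analysed in men who received at least one fraction, grouped by the fractionation they started; men who later stop or change stay in that group; the comparison by randomised arm is reported alongside, with the numbers who never started or started the other schedule.

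The cost is one or two sentences and one extra table, with no new data, since the treatment record shows what was delivered. The downside is that the treated set is not strictly the randomised set and may carry selection if men are switched before starting; reporting both comparisons lets the reader see whether that matters. In an open-label trial the choice is best fixed before toxicity results are seen.

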## Methods/design

### Recruitment and study design

The SHARE study is a prospective, randomized, multi-institutional trial. The protocol was approved by the institutional review boards of two participating tertiary hospitals, the Asan Medical Center and Samsung Medical Center, where it is currently ongoing. A computer-generated randomization schedule assigns the patients to either the HRT (65 Gy in 2.5-Gy fractions) or CRT (66 Gy in 2-Gy fractions) arm (Fig. 1). Random assignment is performed with a 1:1 allocation using blocked randomization, with a random block size of 4. Patients will be stratified by intermediate or high-risk according to the National Comprehensive Cancer Network (NCCN) risk classification [37] using a computer-generated random allocation sequence to ensure concealment. The clinical research nurse keeps the original random allocation sequences using the Excel file locked with a password. The process of allocation concealment from primary researchers and participants is maintained until the time of assignment. Neither the investigators nor the participants are masked to the allocated arm because blinding is not possible. For adequate participant recruitment, the investigators fully explain to potential participants the purpose, design, potential risks, and benefits of this study, as well as general ethical issues. A monthly newsletter regarding participant enrollment will be made and sent to the principal investigator and clinical research coordinators of each institution. All patients must provide written informed consent.

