### Inclusion criteria

Eligible patients are required to have a diagnosis of histologically confirmed prostate adenocarcinoma after radical prostatectomy and must fulfill the following criteria: aged ≥ 19 years, an Eastern Cooperative Oncology Group performance status 0–1, intermediate or high risk according to the NCCN guidelines [37], and total serum PSA level after prostatectomy > 0.2 and ≤ 1.0 ng/ml. Patients should also have adequate bone marrow (absolute neutrophil count ≥ 1500 cells/mm^3^; hemoglobin concentration ≥ 8.0 g/dl; platelet count ≥ 50,000 cells/mm^3^), liver (total bilirubin < 1.5 times the maximum normal value; alanine aminotransferase or aspartate aminotransferase < 2.5 times the maximum normal value), and renal (creatinine < 2.0 ng/dl) function, as assessed by tests performed within the 6-month period prior to enrollment.

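### Baseline values get between-arm significance tests but play no part in the primary bPFS comparison: a modest forgone gain in power, not an error

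*Protocol article*

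**What the plan says.** All of this is in the protocol article.

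- **Patient characteristics** (Sample size considerations and statistical analysis): chi-square and Student's t tests "will be used for categorical and continuous variables of patient characteristics, respectively". In a two-arm trial the natural reading is a comparison between arms.
- **Primary comparison** (same section): Kaplan-Meier curves for bPFS, and "the log-rank test will be used to compare the curves between the two study arms". No stratum, covariate or regression model is mentioned.
- **Design figures** (same section): the target is an "absolute increase in bPFS of 15% (from 50 to 65%) at 5 years". The size is 144 per arm, 288 in all, on the assumption that everyone is followed for five years or more and that 5% are lost. The power claim for that size reads "which achieves 80% power, with a two-sided *α* of 0.05".
- **Randomisation** (Recruitment and study design): "Random assignment is performed with a 1:1 allocation using blocked randomization", stratified by NCCN intermediate or high risk. Risk group also defines a planned subgroup analysis.
- **Entry PSA** (Inclusion criteria): "total serum PSA level after prostatectomy" must lie above 0.2 and at or below 1.0 ng/ml, so every man has a qualifying value within a five-fold range.

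**The concern.** Two stated choices are weaker than they need be.

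First, under 1:1 randomisation any baseline difference between arms is due to chance. A p-value for it tests something already known, and does not show whether the imbalance matters for bPFS. A column of such p-values can also prompt a later adjusted analysis built on whichever variable fell below 0.05.

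Second, the trial holds baseline information likely to bear on the endpoint, and the primary comparison as written uses none of it. That includes the NCCN group by which patients were randomised. It also includes the entry value of PSA, the marker on which biochemical progression is defined. When a prognostic variable is left out of a time-to-event comparison, the marginal treatment effect is diluted relative to the effect among men with the same prognosis. Some power is then left unused. The trial is sized at about 80% with little to spare, so even a few points have some value.

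**Working it through.** **Step 1. Reproduce the stated size for the unadjusted log-rank test.**

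- Hazard ratio under proportional hazards: ln 0.65 / ln 0.50 = 0.6215.
- Events (Schoenfeld, 1:1, two-sided 0.05, 80% power): 4 × (1.960 + 0.842)² / (ln 0.6215)² = 139.
- Accrual is about 2.58 years (August 2019 to March 2022, Trial status), so follow-up runs from 5 to 7.58 years. With exponential event times, rates are ln 2 / 5 = 0.1386 per year (CRT) and −ln 0.65 / 5 = 0.0862 per year (HRT). Averaging 1 − exp(−rate × t) over t from 5 to 7.58 gives 0.580 and 0.417, mean 0.498.
- N = 139 / 0.4984 = 278.9; divided by 0.95, about 294. This is within 3% of 288.
- Power at 288 × 0.95 = 273.6 patients: 273.6 × 0.4984 = 136.4 events; 0.4756 × √136.4 / 2 − 1.960 = 0.817, which is 79.3%.

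This counts follow-up beyond 5 years. If everyone were followed for exactly 5 years, the mean event probability would be (0.50 + 0.35) / 2 = 0.425 and power about 73%. That is a separate matter from this point.

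**Step 2. Gain from adjustment, by simulation.** Common settings: 274 evaluable patients, exponential event times, marginal 5-year bPFS held at 50% and 65%, minimum 5-year follow-up. The unadjusted log-rank test is compared with the Wald test for arm in a Cox model containing the covariate. Prognostic strength is an assumption throughout.

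*Qualifying PSA alone.* Log2 PSA is uniform from 0.2 to 1.0, which spans log2 5 = 2.32 doublings, with SD 2.32 / √12 = 0.67. Accrual 32 months, 4000 trials per setting.

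| Assumed HR per doubling | Unadjusted | Adjusted |
|---|---|---|
| 1.2 | 79% | 79% |
| 1.5 | 80% | 81% |
| 2.0 | 79% | 83% |

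*One combined normal score.* Accrual 2.58 years, 3000 trials per setting.

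| Assumed HR per SD | HR for arm given the score | Unadjusted | Adjusted |
|---|---|---|---|
| 1.0 | 0.621 | 80.1% | 79.6% |
| 1.3 | 0.616 | 79.8% | 81.0% |
| 1.5 | 0.608 | 79.1% | 82.3% |
| 2.0 | 0.582 | 78.1% | 87.2% |

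The Monte Carlo standard error near 80% power is √(0.8 × 0.2 / 3000) = 0.7 points, or 0.6 points with 4000 trials.

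*Hand check.* Put the conditional hazard ratio into the Step 1 power formula with about 136 events. For 0.608: 0.498 × 11.68 / 2 − 1.96 = 0.95, or 83%. For 0.582: 0.541 × 11.68 / 2 − 1.96 = 1.20, or 88%. Both are close to the simulated values. They are slightly high, because a spread of hazards lowers the number of events after year 5.

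*Consistency.* An HR of 2.0 per doubling of PSA is exp(0.693 × 0.67) = 1.59 per SD. Its 4-point gain fits the second table.

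**Step 3. Type I error.** With the combined score the null rejection rate was 4.5% to 5.7% across settings for both tests (standard error 0.4 points). A further setting with log-hazard SD 0.75 gave 5.1% unadjusted and 5.3% adjusted.

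**Step 4. Chance findings among baseline tests.** If 10 to 15 independent variables were tested, at least one p < 0.05 would arise by luck with probability 1 − 0.95^10 = 0.40 to 1 − 0.95^15 = 0.54. The number of variables is an assumption, and real baseline variables are correlated.

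**The case against.** The case against is substantial. An unadjusted log-rank test is a standard, valid primary analysis, and covariates for a supportive model are commonly left to an SAP, which is not shown here. The proposed hazard ratio is conditional, whereas the design effect is the marginal 50% versus 65%. Most of this stands. It is why the point is an improvement to stated methods and why the log-rank test stays. It does not rescue the baseline tests, which the article affirmatively plans.

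A reader might infer more than the documents support:

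- *That the trial is underpowered because it does not adjust.* The size was set for an unadjusted comparison and roughly delivers its stated power on that basis.
- *That baseline data serve only for significance tests.* NCCN group stratifies randomisation and defines a subgroup.
- *That the primary result is open to data-driven choice.* The primary test is fixed as a log-rank test, and nothing says that baseline p-values select covariates. The risk concerns only adjusted analyses added later. The 40% to 54% figure describes chance imbalance, not bias in the primary test.
- *That the gain is large.* Adjusted power reaches 89% and 93% if one known, correctly modelled score has log-hazard SD 0.75 or 1.0 (HR per SD exp(0.75) = 2.12 and exp(1.0) = 2.72). The documents give no basis for that strength. A real model would have to estimate several effects, and the simulations contain no NCCN stratum.
- *That the Background section supplies the strength.* Its high-risk features concern PSA rise after surgery, which every enrolled man has already had. Its PSA threshold of 20 ng/mL is not the entry value of 0.2 to 1.0 ng/ml, and that narrow window may limit what PSA adds.

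**Conclusion.** The point holds as an efficiency and pre-specification improvement. The planned tests of patient characteristics are uninformative between randomised arms. The log-rank test is valid, with about the stated 80% power when follow-up beyond 5 years is counted, but it forgoes a gain available from data the trial must already hold to enrol and randomise.

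That gain is about 0 to 4 points of power for qualifying PSA alone (HR 1.2 to 2.0 per doubling) and about 1 to 9 points for a combined score (HR 1.3 to 2.0 per SD). If the covariate has no prognostic value, power is essentially unchanged (80.1% against 79.6%, within simulation error). These figures rest on assumed prognostic strength, exponential event times, proportional hazards given the covariate, and a correctly specified covariate effect.

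**What to change.** In the statistical analysis section:

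1. Describe patient characteristics by arm and remove the chi-square and t tests of them.
2. Before any outcome data by arm are seen, pre-specify a Cox analysis of bPFS with arms as randomised. Stratify by or adjust for NCCN risk group, and adjust for the log of the PSA value that qualified the man for entry. Add Gleason group and pathological T stage if they are recorded. Report the hazard ratio with its 95% CI.
3. Keep the log-rank test and the Kaplan-Meier difference at 5 years alongside, so that the marginal effect used in the design is still reported. State which analysis is primary.
4. Do not adjust for ADT or radiotherapy field choices made after allocation.

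The cost is analysis wording. No new patients are needed, and NCCN group and qualifying PSA are already required at entry. The data collection section does not name T stage, so its availability should be checked. The hazard ratio becomes conditional on the listed covariates and relies on proportional hazards; the log-rank test and the 5-year difference serve as the check. On the article's own dates, the last patients reach five years in about 2027, so at publication there was time to fix this ahead of the planned analysis.

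### Randomisation is stratified by NCCN risk group, but the primary log-rank test names no strata; run as written it is valid, mildly conservative, and forgoes a small gain in power

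*Protocol article*

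**What the plan says.** Under Recruitment and study design, the article sets out the allocation: "Random assignment is performed with a 1:1 allocation using blocked randomization, with a random block size of 4". It then names the one stratification factor: "Patients will be stratified by intermediate or high-risk according to the National Comprehensive Cancer Network (NCCN) risk classification".

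Under Sample size considerations and statistical analysis, the bPFS curves are estimated by Kaplan–Meier and "the log-rank test will be used to compare the curves between the two study arms". No strata and no covariates are attached to that test. Risk group appears in that section only here: "Subgroup analyses will be performed based on the risk group (intermediate vs. high-risk group", alongside field size and androgen deprivation therapy.

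The design target is marginal, stated for each arm as a whole: "Power calculations are based on an absolute increase in bPFS of 15% (from 50 to 65%) at 5 years". The resulting size is given in these words: "at least 144 patients per treatment arm (288 patients in total) are required". Behind that number stand a shortest follow-up of five years, an allowance of 5% for patients lost, a target power of 80% and a two-sided 5% significance level.

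**The concern.** Blocking within risk group forces the arms to be nearly balanced on it. If risk group predicts biochemical failure, chance imbalance on it would otherwise be part of the sampling variation of the log-rank statistic. The design removes that part, but the variance formula of an unstratified log-rank test still counts it. The standardised statistic is then less variable than its reference distribution, so a nominal 5% test rejects less than 5% of the time under the null.

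At stake is efficiency: a test that uses the stratification reaches its nominal level and has somewhat more power from the same patients. There is also a matter of clarity. The trial is open-label, and two defensible p-values would exist without this text saying which one is primary.

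**Working it through.** **1. Reproduce the plan's own figure with an ordinary log-rank calculation.**

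Inputs from the article: 5-year bPFS 50% and 65%, two-sided alpha 0.05, power 80%, minimum follow-up 5 years, loss 5%. Trial status gives recruitment from August 2019 to March 2022, 31 months or 2.58 years. Exponential survival and uniform accrual are assumed.

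- Hazard ratio: ln(0.65)/ln(0.50) = 0.621.
- Events (Schoenfeld): 4 × (1.960 + 0.842)² / (ln 0.621)² = 138.8, so 139.
- Hazards per year: −ln(0.50)/5 = 0.1386 and −ln(0.65)/5 = 0.0862.
- Event probability with hazard λ, accrual A and minimum follow-up F = 5: 1 − [exp(−λF) − exp(−λ(F + A))]/(λA). With A = 2.58 this gives 0.580 and 0.417, mean 0.498.
- Per arm: 139/0.498/2 = 139.4; dividing by 0.95 gives 146.8, so 147.
- With A = 3 years (assumed) the mean event probability is 0.509, and the result is 143.7, so 144.

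The stated 144 per arm is therefore reproduced exactly at 3 years' accrual and within about 2% at 2.58 years. Analytic power with 288 × 0.95 patients is 79.3% and 80.1% respectively. The sample size is consistent with an ordinary log-rank test.

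**2. Compare the unstratified and stratified tests by simulation.**

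Settings: 288 patients, permuted blocks of 4 within two strata, 2.58-year accrual, 5-year minimum follow-up, 5% loss, exponential survival within stratum. The marginal 5-year bPFS is held at 50% versus 65% for power; alpha is obtained with no treatment effect. The prognostic hazard ratio (high versus intermediate) and the share of high-risk patients are assumptions.

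| Prognostic HR | High risk | Alpha, unstratified | Alpha, stratified | Power, unstratified | Power, stratified | Gain (points) |
|---|---|---|---|---|---|---|
| 1.0 | 50% | 0.053 | 0.053 | 0.797 | 0.796 | nil |
| 1.5 | 50% | 0.050 | 0.054 | 0.803 | 0.811 | 0.8 |
| 2 | 50% | 0.044 | 0.051 | 0.804 | 0.823 | 1.9 |
| 2 | 70% | 0.043 | 0.049 | 0.799 | 0.812 | 1.3 |
| 3 | 50% | 0.033 | 0.051 | 0.802 | 0.853 | 5.1 |
| 3 | 70% | 0.038 | 0.049 | 0.800 | 0.830 | 3.0 |
| 4 | 50% | 0.025 | 0.048 | 0.806 | 0.875 | 6.9 |

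The 50% rows at HR 1.5, 2 and 3 use 25,000 replicates (Monte Carlo standard error about 0.0014 for alpha and 0.0025 for power). The others use 8,000 (about 0.0024 and 0.0045). A separate run with 60% high risk agrees: unstratified alpha is about 4.4% at HR 2 and 3.3% at HR 3, with gains of about 1.7 and 4.7 points, about 0.7 at HR 1.5, and none at HR 1.

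**3. Why unstratified power stays at about 80%.**

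The marginal 50% versus 65% is fixed, so the unstratified test faces the same marginal contrast in every row. The treatment hazard ratio within strata that produces this contrast moves further from 1 as the strata separate: 0.621 at prognostic HR 1, 0.612 at HR 2, 0.597 at HR 3 (50% high risk). The stratified test picks up that stronger within-stratum effect, so its advantage lies above the planned power.

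**The case against.** The strongest objection is that the point rests on silence. The article does not call the test unstratified, it condenses a fuller protocol, and strata are often fixed in an analysis plan that is not shown here. That stands as a limit: it cannot be asserted that the final analysis will be unstratified. What remains is that the article does name its primary test, names it without strata, and gives a sample size that fits the ordinary form. Stratifying that named test is a better choice at no cost, and if the analysis plan already has it, one clarifying sentence brings the two into line.

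A second objection is that the size depends on a prognostic effect the documents do not give. This also stands. The Background reports that about one-third of men recur within a decade of prostatectomy, against more than 60% with high-risk features. If the horizons were alike, ln(0.40)/ln(0.67) gives about 2.3. But the horizon of the second figure is not stated, the comparison is with all men, and it concerns recurrence after surgery, which every participant here has already had. It makes an HR of 2 to 3 plausible and no more.

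A reader might also infer four stronger things that the documents do not support:

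- **That the planned power is lost.** Unstratified power is 79.7% to 80.6% in every row of the table.
- **That the test is invalid.** The error is on the conservative side; type I error is not inflated.
- **That the treatment effect is estimated with bias towards the null.** The analysis section names no hazard ratio, and marginal and within-stratum hazard ratios are different estimands, neither a faulty version of the other.
- **That distant metastasis-free and cancer-specific survival suffer to the same degree.** Their log-rank tests are also named without strata, but no event rates or prognostic effects are available, so no size can be given.

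**Conclusion.** The point holds as a minor matter of efficiency and consistency between design and analysis. If the primary log-rank test is run without strata, as written, it is valid and mildly conservative to the extent that NCCN risk group predicts bPFS after salvage radiotherapy. At an assumed prognostic HR of 2 to 3, true alpha is about 4.4% to 3.3% and about 1 to 5 points of available power are forgone; at 1.5 it is about 1 point, and at 1 nothing. The trial's planned power of about 80% is intact.

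The direction is secure. The size rests on the assumed prognostic HR, the assumed share of high-risk patients (50% to 70%), exponential survival within stratum, and proportional hazards.

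**What to change.** State in the analysis section that the primary bPFS comparison is a log-rank test stratified by NCCN risk group (intermediate versus high) as recorded at randomisation. State that any hazard ratio reported with it comes from a Cox model stratified by the same factor, and that the unstratified log-rank test is kept as a sensitivity analysis. If the analysis plan already says this, align the protocol wording with it. Settle it before any comparison of the arms, since the trial is open-label.

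The cost is one sentence. The variable is already recorded for randomisation, no further data or patients are needed, and the sample size stays at 288. With two strata and about 139 events there is no material downside: where risk group has no prognostic value, power is unchanged within simulation error (79.7% versus 79.6%).
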